### 2.8. Process Evaluation

The process evaluation for both the MTM-based and knowledge-based intervention groups will utilize tools developed based on the RQFSM model [19]. These tools include the Reach Evaluation Tool, which assesses the intervention’s ability to engage the target population; the Quality Evaluation Tool, which evaluates the delivery and content quality; and the Fidelity Evaluation Tool, ensuring that interventions are implemented as designed. Additionally, the Satisfaction Evaluation Tool will measure participant satisfaction with the intervention experience, while the Management Evaluation Tool will monitor the overall coordination and management of the intervention process. Together, these tools provide a comprehensive evaluation to assess both the implementation and impact of the intervention.

### 2.9. Instrumentation

The survey tool for this research consists of a 54-item questionnaire (Supplement S4) specifically designed and refined through a meticulous two-stage review process conducted by a panel of six experts. These specialists, with expertise in MTM theory, instrumentation, and the target population, evaluated the questionnaire’s face and content validity in two rounds. They assessed the clarity, readability, and relevance of the items, leading to wording adjustments and the removal of one item from the behavioral confidence section. Following these revisions, the panel reached a unanimous agreement on the adequacy of the content and face validity for each MTM subscale. The finalized instrument achieved a Flesch Reading Ease score of 57.4 and a Flesch–Kincaid Grade Level of 8.7, confirming its suitability for the intended audience. In prior studies utilizing this MTM-based instrument among college populations, internal consistency estimates (Cronbach’s alpha) for the subscales ranged from 0.76 to 0.89, indicating acceptable to strong reliability [11].

Participants in this study must complete the 54-item survey based on the Multi-theory Model (MTM) at three time points: before the intervention (pre-test), immediately after the intervention (post-test), and during the follow-up period at eight weeks post-intervention. Prior to participation, all individuals will be required to provide informed consent by signing a consent form. This ensures that the participants understand the purpose of this study, their role, and their rights, including confidentiality and voluntary participation.

The initial questions of the survey focus on the frequency and types of gambling activities the participants had engaged in over the past 30 days. These questions are essential for establishing baseline measurements and serve as screening criteria for this study. The participants are asked to report the number of days they gambled during this period and to specify the types of gambling activities they participated in, such as lotteries, sports betting, poker, and online gambling. This information helps to categorize the participants based on their gambling behavior and ensures that the sample includes individuals who are actively engaged in gambling.

After the baseline questions, the survey includes the Problem Gambling Severity Index (PGSI) to assess the impact of gambling on various aspects of the participants’ lives over the past 12 months. This section consists of nine questions designed to evaluate the severity of gambling-related issues by examining factors such as financial strain, emotional distress, health complications, and social consequences linked to gambling behaviors. The participants rate their experiences on a scale from 0 (“Never”) to 3 (“Almost always”), providing a detailed measure of the extent to which gambling has affected their lives. This information helps classify participants as low-risk, moderate-risk, or problem gamblers based on their responses. The Problem Gambling Severity Index (PGSI) is a widely used and validated measure of gambling-related risk and severity. As a part of the Canadian Problem Gambling Index, it is commonly used in both general and college populations. The PGSI has demonstrated strong internal consistency in previous studies, with reported Cronbach’s alpha values typically ranging from 0.84 to 0.91, supporting its reliability as a measure of gambling-related risk behaviors [20].

The third section of the survey consists of 32 questions aimed at assessing the constructs of the Multi-theory Model (MTM) for both the initiation and sustenance of behavior change. These questions explore the participants’ readiness to initiate responsible gambling behaviors and the strategies they employ to maintain these behaviors over time. By focusing on the psychological, social, and environmental factors that influence behavior change, this section provides valuable insights into participants’ motivation, confidence, and commitment to adopting and sustaining responsible gambling practices. The final section of the survey collects demographic information, such as age, gender, and educational background, ensuring a thorough understanding of the participant population and enabling more accurate data analysis.

### 2.10. Data Analysis

The primary objective of this study is to evaluate the efficacy of an MTM-based intervention [10] in promoting responsible gambling behaviors among college students. The intervention is designed to help participants recognize the advantages of responsible gambling while addressing common barriers, enhance participatory dialogue, build behavioral confidence, and facilitate changes in their physical and social environments. Additionally, the intervention aims to foster emotional transformation and implement strategies for maintaining responsible gambling behavior over time. Data analysis will be conducted using SAS 9.4 (SAS Institute Inc., Cary, NC, USA), with a significance level of 0.05 for all statistical analyses to determine the effectiveness of the intervention. This will allow for a comprehensive evaluation of how the MTM-based approach impacts gambling behaviors and the sustainability of responsible gambling habits in the target population.

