### 2.3. Sample Size Calculation

A power analysis was conducted using G*Power (version 3.1) [18] to estimate the required sample size for this study. Based on a Two-Way Mixed Analysis of Variance (ANOVA) with a medium effect size of 0.30, two intervention groups, three time points (pre-, post-, and follow-up), an alpha level of 0.05, and a beta of 0.20 (80% power), the analysis assumed a correlation of 0.5 among repeated measures and applied a non-sphericity correction of 1. The calculation indicated a required sample size of 20 participants per group. To account for potential attrition and missing data, the sample size was increased by 50%, resulting in a total of 60 participants, with 30 in each group.

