### 2.11. Per-Protocol Analysis

A per-protocol (PP) analysis may be conducted to evaluate the efficacy of the RESPONSIBLEPLAY^©^ MTM-based intervention under optimal conditions [21]. This analysis includes only those participants who fully comply with the intervention protocol and complete the follow-up assessments. By focusing on this subset of participants, the PP analysis aims to provide a more precise estimate of the intervention’s efficacy. Participants will be included in the PP analysis if they meet the following criteria:Absence of Major Protocol Violations: The participants must strictly adhere to the predefined inclusion criteria and avoid any significant deviations from the study protocol [21].Completion of Prescribed Intervention: Only participants who complete their assigned intervention as designed must be considered [21].Availability of Primary Outcome Data: The participants must have complete data for the primary outcome measure to be included in the analysis [21].

The per-protocol (PP) analysis seeks to confirm the efficacy of the interventions by excluding participants who fail to adhere to the protocol or do not complete this study. This approach ensures that the observed effects can be directly attributed to the interventions, focusing only on the participants who fully comply with the study design. In contrast, the intention-to-treat (ITT) analysis includes all randomized participants, regardless of their adherence to the protocol, providing a more conservative estimate of treatment efficacy. Together, these complementary methods offer a comprehensive view of the intervention’s impact under both optimal and real-world conditions [21].

The decision to conduct only a PP analysis is based on the goal of evaluating the intervention’s efficacy under ideal conditions, where adherence to the protocol is maximized. By focusing exclusively on the participants who strictly follow the study protocol, the PP analysis eliminates the confounding effects of non-adherence or protocol deviations. This approach provides a clearer understanding of the potential benefits of the RESPONSIBLEPLAY^©^ MTM-based intervention. It is particularly suitable for assessing health behavior interventions, as the impact of such interventions can be more accurately observed in a population that fully adheres to the prescribed protocol [21].

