### 3.1. Significance and Implications

This study addresses a critical gap in the literature by applying MTM constructs to promote responsible gambling behaviors among college students. Unlike knowledge-based interventions that often focus solely on raising awareness without facilitating lasting behavioral change, the MTM-based approach incorporates actionable strategies that aim to not only initiate but also sustain changes in gambling behavior. Through activities such as photovoice, journaling, and role-playing, the participants are equipped with practical tools to recognize, plan for, and maintain responsible gambling habits. These hands-on strategies encourage active participation and empower individuals to take ownership of their behavior, fostering long-term outcomes.

The anticipated outcomes of the RESPONSIBLEPLAY^©^ intervention include improvements in Problem Gambling Severity Index (PGSI) scores and enhanced MTM construct scores, thus validating the framework’s effectiveness for addressing gambling-related issues. By integrating both theoretical and practical components, the intervention ensures it can be adapted for diverse populations, settings, and types of gambling behaviors. For instance, strategies like limiting physical access to gambling opportunities or fostering peer support networks are flexible and applicable across various cultural and socioeconomic contexts, making the RESPONSIBLEPLAY^©^ intervention a potentially scalable and sustainable solution for addressing gambling issues on a broader scale.

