This study relies on the PGSI as one of the key outcome measures. While the PGSI is a widely validated and commonly used instrument, its 12-month recall period may limit its sensitivity to detecting short-term behavioral changes resulting from the intervention. To address this, we will supplement our analyses with MTM construct scores, which are specifically designed to measure short-term behavioral initiation and sustenance. Additionally, we will conduct item-level analyses of the PGSI responses (e.g., related to gambling expenditure, time lost, or emotional impact) to assess whether certain dimensions demonstrate greater sensitivity to short-term change. While the PGSI was selected for its classification utility and comparability across studies, we acknowledge that it is best suited for long-term assessments. Accordingly, we are also exploring the feasibility of a 6- to 12-month follow-up study to better align with the PGSI’s recall window and to assess sustained changes in gambling behavior. This extension will depend on participant retention and funding availability but would provide a more complete evaluation of the intervention’s longitudinal impact.

While simple randomization is used for group assignment, we acknowledge that this method may result in imbalances in baseline characteristics, particularly in smaller samples. Although reproducibility was ensured through the use of a fixed seed in SAS, future studies may benefit from using stratified or block randomization to enhance group comparability.

Lastly, the self-reported nature of gambling behaviors, while necessary for understanding personal habits and attitudes, introduces the potential for recall and social-desirability biases. The participants may underreport or overreport their gambling behaviors due to memory lapses or the desire to present themselves in a more socially acceptable light. To address these biases, future studies could incorporate objective measures or third-party reports to provide a more accurate assessment of gambling behaviors and the intervention’s impact.

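### Effectiveness is tested at an unadjusted 0.05 on the PGSI and six MTM constructs with no ranking, and the primary outcome used for per-protocol entry is never named

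*Protocol article*

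**What the plan says.** Section 2.10 of the protocol article fixes the level: SAS will be used "with a significance level of 0.05 for all statistical analyses to determine the effectiveness of the intervention". It gives a primary objective, but no primary measure, time point or contrast, and no adjustment for multiple tests.

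Section 2.13 and Table 3 apply the two-way mixed ANOVA to the PGSI and the MTM construct scores on an equal footing. Both within-subject and between-group effects are to be read, and neither is named as decisive. The Abstract counts six constructs. The sample size in section 2.3 is tied to no particular outcome.

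Section 2.11 then relies on a primary outcome as an operating rule for the per-protocol set: "The participants must have complete data for the primary outcome measure to be included in the analysis". No section identifies that measure. The nearest statement, in section 3.2, puts the PGSI among several: "This study relies on the PGSI as one of the key outcome measures". Section 3.1 lists as anticipated outcomes "improvements in Problem Gambling Severity Index (PGSI) scores and enhanced MTM construct scores", again without an order.

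**The concern.** There are two problems, and they should be kept apart.

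The first is error control. Seven outcomes of equal standing are each tested at 0.05, and nothing says which result, or how many, would make the intervention effective. The chance that at least one favours a difference when none exists is then well above 5%.

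The second is what a positive result would mean. Table 2 assigns each component of the experimental programme to an MTM construct, while the comparison group receives lectures. A construct score may therefore truly differ because it was taught. Section 3.2 concedes that the 12-month recall of the PGSI may blunt it to short-term change and answers by leaning on the construct scores. Without a hierarchy, one construct could carry an efficacy claim while gambling itself has not changed.

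**Working it through.** **Inputs**
- Level per test: 0.05 (section 2.10).
- Outcomes: PGSI plus six constructs = 7 (Abstract, section 2.13, Table 3). This assumes one score per construct.
- Simulation setting: 20 per group and three time points, with the section 2.3 assumptions ("the analysis assumed a correlation of 0.5 among repeated measures and applied a non-sphericity correction of 1"). Whether 20 per group follows from the inputs in section 2.3 is a separate question.
- Correlation between outcomes: not given in the article. Assumed here as 0.3 to 0.8 within a scale and 0.1 to 0.6 between a PGSI item and a construct.

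**1. One outcome, one test.** The simulated null rate for the group-by-time interaction is 4.9% to 5.2%, so the plan's 5% is reproduced for a single test.

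**2. Seven independent outcomes, one between-arm test each.** P(at least one) = 1 − (1 − 0.05)^7 = 1 − 0.698 = 30.2%.

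**3. Either the group effect or the interaction may count.** This gives 2 × 7 = 14 tests: 1 − 0.95^14 = 51.2% if independent.

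**4. Correlated outcomes.** The mixed ANOVA was simulated with no true difference, 10,000 trials per row (Monte Carlo standard error at most √(0.25/10,000) = 0.5 percentage points). The PGSI total was formed as the sum of nine items.

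| Correlation within scale / between item and construct | Interaction only | Group effect or interaction |
|---|---|---|
| 0 / 0 | 29.7% | 50.9% |
| 0.3 / 0.1 | 27.9% | 47.1% |
| 0.5 / 0.3 | 24.5% | 42.2% |
| 0.6 / 0.4 | 21.2% | 38.1% |
| 0.8 / 0.6 | 16.3% | 29.7% |

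A second run of the interaction test gave all seven outcomes one common correlation. The rate was 27.5% at 0.3, 24.1% at 0.5, 18.4% at 0.7 and 11.9% at 0.9. Even the last is 11.9/5 = 2.4 times nominal.

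**5. After naming one primary outcome and one deciding contrast.** There is one test at 0.05, so the rate is 5%. Holm over the six constructs starts at 0.05/6 = 0.0083 for the smallest p-value.

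These rates describe chance findings only. They do not measure the second problem, in which a construct truly moves because it was taught.

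**The case against.** The strongest reply is that multiplicity rules and the naming of a primary outcome often sit in a full protocol, an analysis plan or a registration, none of which is shown. That limits the claim to the article. It does not remove it, because the article does not defer the matter. It sets one level for every effectiveness analysis and uses the unnamed outcome as a rule.

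It can also be said that no section declares one significant result sufficient, that section 3.1 joins PGSI and construct improvement with an and, and that section 3.2 treats the constructs as a supplement, which hints that the PGSI leads. This is fair, but it is a hint. Section 3.2 stops short of calling the PGSI primary, and no section states a success rule.

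Some stronger readings are tempting and do not hold:
- **Sixteen tests.** A reader might add the nine PGSI items and obtain 1 − 0.95^16 = 56%. Section 3.2 does not say that all nine items are tested or that any item decides effectiveness. The PGSI total is also built from those items, so independence is untenable. The reported alpha of 0.84 to 0.91 implies a mean inter-item correlation, α/(9 − 8α), of 0.84/2.28 = 0.37 to 0.91/1.72 = 0.53.
- **Time effects.** Change over time in both arms is not a false claim that one arm is better, so time tests do not belong in the count.
- **Choosing the analysis set after the results.** A reader might infer this from the unnamed outcome. However, all measures sit in one survey given at the same visits, and section 2.11 also requires completed follow-up. The per-protocol set would be nearly the same whichever measure is primary, apart from item non-response.

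**Conclusion.** The point holds for the article as written. Effectiveness rests on seven unranked outcomes at an unadjusted 0.05, no ANOVA effect is named as decisive, and the primary outcome on which per-protocol entry depends is never identified.

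With one between-arm test per outcome, the familywise error is 30% under independence and about 16% to 28% under the assumed correlations of 0.3 to 0.8. If either the group effect or the interaction may count, it is 51% under independence and about 30% to 47% when correlated. The between-outcome correlations and the one-score-per-construct count are assumptions.

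A reader might infer that a chance verdict of effectiveness is the expected outcome. With one between-arm test for each of the seven outcomes, the figures do not support that: the risk is several times nominal but stays below one half. The second problem, an efficacy claim carried by a taught construct, stands by reasoning and has no error rate attached.

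**What to change.** Before any outcome data are analysed by group, state the following in the protocol and analysis plan:

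1. **Primary outcome.** Name one behavioural measure already collected. The PGSI total is the direct choice, since the planned ANOVA covers it. If the sponsor judges its recall window unsuitable (at eight-week follow-up at most 3 + 8 = 11 of the 52 weeks fall after the intervention starts), use days gambled in the past 30 days, which the same survey records at each visit.
2. **Deciding contrast.** Use the baseline-adjusted group difference at eight weeks, two-sided 0.05.
3. **Section 2.11.** Insert that same measure in the per-protocol criterion.
4. **Secondary.** Test the six MTM constructs with Holm adjustment at 0.05.
5. **Exploratory.** Give this label to the PGSI item-level analyses.
6. **Conclusion.** Base the efficacy claim on the primary outcome only.

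The cost is wording and fewer secondary results that can be called significant. No participants or visits are added. Section 2.3 should be restated for the named contrast. With 20 completers per group, a pre-to-follow-up correlation of 0.5 and 80% power, the normal approximation gives a detectable difference of (1.96 + 0.84) × √(2 × (1 − 0.25)/20) = 2.80 × 0.274 = 0.77 SD.

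Keeping all seven outcomes co-equal would instead need about 0.05/7 = 0.0071 each. Using the inputs of section 2.3 with 40 completers (N = 40, f = 0.30, m = 3 time points, ρ = 0.5), noncentral F power would fall from 99% to 93% for the interaction (λ = f²Nm/(1 − ρ) = 0.09 × 40 × 3/0.5 = 21.6). For the between-group effect it would fall from 62% to 32% (λ = f²Nm/(1 + 2ρ) = 0.09 × 40 × 3/2 = 5.4).

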### 2.11. Per-Protocol Analysis

A per-protocol (PP) analysis may be conducted to evaluate the efficacy of the RESPONSIBLEPLAY^©^ MTM-based intervention under optimal conditions [21]. This analysis includes only those participants who fully comply with the intervention protocol and complete the follow-up assessments. By focusing on this subset of participants, the PP analysis aims to provide a more precise estimate of the intervention’s efficacy. Participants will be included in the PP analysis if they meet the following criteria:Absence of Major Protocol Violations: The participants must strictly adhere to the predefined inclusion criteria and avoid any significant deviations from the study protocol [21].Completion of Prescribed Intervention: Only participants who complete their assigned intervention as designed must be considered [21].Availability of Primary Outcome Data: The participants must have complete data for the primary outcome measure to be included in the analysis [21].

The per-protocol (PP) analysis seeks to confirm the efficacy of the interventions by excluding participants who fail to adhere to the protocol or do not complete this study. This approach ensures that the observed effects can be directly attributed to the interventions, focusing only on the participants who fully comply with the study design. In contrast, the intention-to-treat (ITT) analysis includes all randomized participants, regardless of their adherence to the protocol, providing a more conservative estimate of treatment efficacy. Together, these complementary methods offer a comprehensive view of the intervention’s impact under both optimal and real-world conditions [21].

The decision to conduct only a PP analysis is based on the goal of evaluating the intervention’s efficacy under ideal conditions, where adherence to the protocol is maximized. By focusing exclusively on the participants who strictly follow the study protocol, the PP analysis eliminates the confounding effects of non-adherence or protocol deviations. This approach provides a clearer understanding of the potential benefits of the RESPONSIBLEPLAY^©^ MTM-based intervention. It is particularly suitable for assessing health behavior interventions, as the impact of such interventions can be more accurately observed in a population that fully adheres to the prescribed protocol [21].

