## 2. Materials and Methods

### 2.1. Study Design

This study will implement a three-week, single-blinded educational randomized controlled trial (RCT), followed by an eight-week follow-up phase (ClinicalTrials.gov number: NCT06642155). The RCT design, widely recognized as the gold standard for evaluating intervention efficacy, was selected for its ability to minimize bias and establish causal relationships between the intervention and its outcomes through randomization [12]. To ensure methodological rigor and transparency, this study will adhere to the CONSORT checklist for RCTs [13], maintaining high standards of reporting throughout the research process. Figure 1 presents the CONSORT flow diagram.

To evaluate changes in health behavior among the participants, this study will administer pre-, post-, and follow-up assessments using the Multi-theory Model (MTM) constructs [10] and the Problem Gambling Severity Index (PGSI) [14]. The participants will be randomly assigned to one of two groups: the experimental group, which will receive the RESPONSIBLEPLAY^©^ MTM-based intervention, or the comparison group, which will receive a knowledge-based intervention. Random assignment, a fundamental component of RCTs, ensures that all the participants have an equal likelihood of being placed in either group. This approach minimizes selection bias, enhances the validity of the findings [15], and helps balance both known and unknown confounders between groups. Consequently, any observed differences in outcomes can be confidently attributed to the intervention rather than to pre-existing disparities [15]. Figure 2 presents an overview of the study design for evaluating the efficacy of responsible gambling interventions.

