### 3.2. Limitations

While this study introduces a robust framework for promoting responsible gambling behaviors, several limitations must be acknowledged regarding its implementation. First, the reliance on a convenience sample from a single southwestern university may limit the generalizability of the findings. The specific gambling behaviors and environmental influences experienced by the participants may not fully represent those of college students in other regions or demographics. To enhance the external validity of this study, future research should aim to replicate this study across diverse populations and settings to better assess its broad applicability. Additionally, the participants who complete all sessions and follow-up assessments may represent a more motivated or problem-aware subgroup, which could introduce interpretive bias. To address this concern, we will compare baseline characteristics between completers and non-completers to assess the presence of any systematic differences and report these findings transparently in future publications.

This study’s three-week intervention period, although consistent with similar behavior change interventions, may not fully capture the long-term sustainability of responsible gambling behaviors. The eight-week follow-up provides some insight into short-term changes; however, extended longitudinal studies are needed to evaluate the persistence of behavior change and the intervention’s capacity to prevent relapse over time.

Participant attrition remains a significant concern in multi-session interventions, particularly within college populations. While we increased the initial sample size by 50% to accommodate the expected dropout, we acknowledge that actual attrition may exceed this estimate. To address this, we have incorporated several retention strategies, including flexible scheduling, frequent reminders (via email), and graduated incentives to encourage session attendance and follow-up completion. We will transparently report attrition rates at each study phase and perform sensitivity analyses comparing baseline characteristics between completers and non-completers. This will help assess whether retention introduces systematic bias—particularly the concern that the participants who complete all the sessions may represent a more motivated or problem-aware subgroup. These insights will be critical in informing the design and scalability of future studies.

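### Section 2.11 contradicts itself on the analysis set and ends by choosing a per-protocol-only efficacy analysis, which gives up the randomised comparison on which the trial's causal claim rests

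*Protocol article*

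**What the plan says.** All references are to the protocol article.

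- **Section 2.11, opening:** PP is optional: "A per-protocol (PP) analysis may be conducted to evaluate the efficacy".
- **Section 2.11, PP set:** "This analysis includes only those participants who fully comply with the intervention protocol and complete the follow-up assessments". A further criterion reads "The participants must have complete data for the primary outcome measure to be included in the analysis".
- **Section 2.11, second paragraph:** ITT is described as covering all randomised participants, and of the two analyses it says "Together, these complementary methods offer a comprehensive view".
- **Section 2.11, last paragraph:** "The decision to conduct only a PP analysis is based on the goal of" assessing efficacy where adherence is maximised. It adds that this removes the confounding caused by non-adherence.
- **Section 2.13 and Table 3:** the mixed ANOVA and the conditional ANCOVA are named without an analysis set.
- **Section 2.1:** thanks to random assignment, "any observed differences in outcomes can be confidently attributed to the intervention rather than to pre-existing disparities".
- **Section 3.2:** "participants who complete all sessions and follow-up assessments may represent a more motivated or problem-aware subgroup". The response is to report attrition and to compare the baseline characteristics of completers and non-completers.

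**The concern.** The three statements in Section 2.11 (PP optional, PP and ITT together, PP alone) cannot all hold. The last is the only one worded as a decision and the only one given a rationale. If it is followed, anyone who misses part of the programme or the follow-up leaves the analysis.

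The rationale is mistaken. Adherence happens after randomisation and can be affected by the assigned arm. Comparing the adherers of one arm with the adherers of the other is therefore not a randomised comparison, and conditioning on adherence can introduce confounding that randomisation had prevented. Aiming at efficacy under ideal adherence does not rescue it: a plain comparison of each arm's completers does not estimate that effect without a method that deals with selection, and none is planned.

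At stake is the claim in Section 2.1 that differences can be put down to the intervention. The choice also cannot credibly be settled once results are known.

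**Working it through.** **1. Is an all-randomised analysis promised anywhere?** Section 2.11 describes ITT but does not commit to it. Section 2.13 and Table 3 name models only. Section 3.2 promises descriptive comparisons. The answer is no.

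**2. Can the arms plausibly differ in who completes?**
- Section 2.7, as written, pays the experimental arm USD 20 after each of three sessions and again at follow-up: 4 × 20 = USD 80. The comparison arm receives one USD 20 card at the end of follow-up.
- Section 2.4 sends additional reminders to the experimental arm only.
- The sessions differ in kind: role-play, psychodrama and journaling against lectures and presentations.

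**3. How much loss does the design allow?** Section 2.3 raises 40 to 60, so 1 − 40/60 = 33% of those randomised may fall outside the analysis. This is a tolerance, not a forecast.

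**4. How large could the bias be?** The document gives no retention by arm and no link between motivation and outcome, so these inputs are assumptions.

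Let there be no true effect. A participant completes when a latent propensity exceeds the threshold that gives completion proportion p. The propensity correlates c = 0.8 with motivation, and motivation correlates r = 0.3 or 0.5 with improvement. Among completers, mean improvement is shifted by c × r × λ(p) SD, where λ(p) = φ(z_p)/p and z_p is the standard normal quantile of p. The bias (experimental minus comparison) is c × r × [λ(p_E) − λ(p_C)].

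Values: λ(0.80) = 0.350, λ(0.53) = 0.751, λ(0.90) = 0.195, λ(0.60) = 0.644.

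| Completion, experimental vs comparison | r = 0.3 | r = 0.5 |
|---|---|---|
| 80% vs 53% (24 and 16 of 30) | 0.24 × (0.350 − 0.751) = −0.10 | 0.40 × (−0.401) = −0.16 |
| 90% vs 60% (27 and 18 of 30) | 0.24 × (0.195 − 0.644) = −0.11 | 0.40 × (−0.449) = −0.18 |
| 53% vs 80% | +0.10 | +0.16 |
| 67% vs 67%, same mechanism | 0 | 0 |

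Positive values favour the intervention. The arm that retains fewer people keeps the more strongly selected, more motivated ones, so its mean is pushed up.

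Simulation with 30 per arm and a two-sided t-test at 5% agrees. Type I error is about 6% to 9% for the two unequal splits and about 5% with equal retention and a common mechanism.

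**5. Sensitivity to the assumptions.** If motivation alone decides completion (c = 1), 80% vs 53% gives 0.12 to 0.20 SD. Equal retention does not guarantee safety: at 67% in both arms, with c = 0.8 in one and 0.2 in the other, the bias is (0.8 − 0.2) × r × λ(0.67) = 0.6 × r × 0.541, or 0.10 to 0.16 SD.

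**6. Do the planned safeguards correct the estimate?** Comparing completers with non-completers at baseline describes selection but leaves the effect estimate unchanged. The ANCOVA in Section 2.13 is used only if a baseline difference is significant, and it adjusts only for measured variables.

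**The case against.** Four points can be made for the plan.

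**The text does not say only PP throughout, and selection is disclosed.** Both are true. The earlier sentences of Section 2.11 leave room for ITT, and Section 3.2 names the completer problem openly. But the explicit decision is PP alone, and disclosure does not change the estimate.

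**The bias figures are hypothetical.** This stands. They rest on assumed retention gaps of 27 to 30 percentage points and assumed correlations, and they vanish with equal retention and a common mechanism. Bias is a risk here, not a demonstrated result.

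**A reader might infer that PP would manufacture a positive result.** The document does not support that. The documented differences in payment and reminders would plausibly raise completion in the experimental arm, and under a common mechanism that biases against the intervention. A false positive needs the reverse retention pattern or a selection mechanism that differs by arm. Neither is documented.

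**A reader might also infer that the completer comparison has too little power to be informative.** That does not follow. Under the model above, 40 completers and 20 non-completers differ by about 1.31 SD in motivation. Power to detect this is about 99% if motivation is measured directly, about 80% with a baseline measure correlated 0.6 with it, and 29% with one correlated 0.3. The sound criticism is only that the comparison corrects nothing.

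**Conclusion.** The point holds. Section 2.11 is internally inconsistent, and its final stated decision is a PP-only efficacy analysis of full compliers with complete data. Its claims that this removes confounding and secures direct attribution are wrong, and they undercut the reasoning in Section 2.1. This is a choice that the article states and defends, not a detail left to an unseen analysis plan.

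The size and sign of the bias cannot be derived from the document. Under the stated assumptions it is about 0.10 to 0.18 SD. It goes against the intervention if the experimental arm retains more, in its favour if that arm retains less, and is about zero when retention and mechanism are equal. The plan could therefore mask a real effect as easily as suggest a false one.

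**What to change.** - Rewrite Section 2.11 so that the primary analysis includes all randomised participants in their assigned arm, using a likelihood-based mixed model on every available survey. SAS is already the software, so PROC MIXED will do. State this set in Section 2.13 and Table 3, and keep PP as secondary.
- Delete the rationale for PP alone and the claim that PP eliminates confounding.
- Collect outcomes from everyone randomised. The model alone is valid only under missing-at-random, and it would not remove bias if unmeasured motivation drives missingness. Section 2.4 ties the pre-test to the Week 1 session, the post-test to the Week 3 session and the follow-up to an attended visit, so non-attenders lose data by design. Seek the pre-test from everyone, ideally before or at randomisation, and the post-test and eight-week surveys regardless of session attendance.

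**Cost:** protocol and analysis-plan wording, a small change in data-collection mode for non-attenders (for example an emailed survey link, as participants are already contacted by email), and a reported effect that may be smaller.
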